## Abstract

**Background:**

In children, the prevalence’s of both obesity and asthma are disconcertingly high. Asthmatic children with obesity are characterised by less asthma control and a high need for asthma medication. As the obese asthmatic child is becoming more common in the clinical setting and the disease burden of the asthma-obesity phenotype is high, there is an increasing need for effective treatment in these children. In adults, weight reduction resulted in improved lung function, better asthma control and less need for asthma medication. In children this is hardly studied. The Mikado study aims to evaluate the effectiveness of a long term multifactorial weight reduction intervention, on asthma characteristics in children with asthma and a high body weight.

**Methods/design:**

The Mikado study is a two-armed, randomised controlled trial. In total, 104 participants will be recruited via online questionnaires, pulmonary paediatricians, the youth department of the Municipal Health Services and cohorts of existing studies. All participants will be aged 6–16 years, will have current asthma, a Body Mass Index in the overweight or obesity range, and no serious comorbidities (such as diabetes, heart diseases). Participants in the intervention arm will receive a multifactorial intervention of 18 months consisting of sessions concerning sports, parental involvement, individual counselling and lifestyle advices including dietary advices and cognitive behavioural therapy. The control group will receive usual care. The primary outcome variables will include Forced Expiratory Volume in one second and Body Mass Index - Standard Deviation Score. Secondary outcomes will include other lung function parameters (including dynamic and static lung function parameters), asthma control, asthma-specific quality of life, use of asthma medication and markers of systemic inflammation and airway inflammation.

**Discussion:**

In this randomised controlled trial we will study the potential of a multifactorial weight reduction intervention to improve asthma-related outcome measures in asthmatic children with overweight. Moreover, it will provide information about the underlying mechanisms in the relationship between asthma and a high body weight in children. These findings can contribute to optimal management programs and better clinical guidelines for children with asthma and overweight.

**Trial registration:**

Clinicaltrial.gov NCT00998413

## Background

The increase in childhood obesity in recent decades is a worldwide problem. The global prevalence of overweight and obesity in children increased from 4.2% in 1990 to 6.7% in 2010 [1]. Similar to childhood obesity, the prevalence of childhood asthma has been rising in the previous decades [2]. Asthma is a common chronic disease in children, and accounts for many disability-adjusted life years and considerable medical costs [3].

Several studies demonstrated an association between obesity and childhood asthma [4,5]. A recent meta-analysis by Chen et al. showed a dose-responsiveness of elevated BMI on asthma incidence, expressed as a relative risk (RR) of 1.19 (95%CI: 1.03-1.37) for overweight and a RR of 2.02 (95%CI: 1.16-3.50) for obesity to develop future asthma [5]. Furthermore, obesity is associated with less asthma control and more use of oral corticosteroids [6,7].

Various potential pathophysiological theories have been proposed to explain the association between obesity and asthma. The first theory supports the mechanical effect of obesity on asthma, as obesity can adversely impact lung volumes. It is associated with reductions in Vital Capacity (VC), Forced Expiratory Volume in 1 second (FEV_1_) and Expiratory Reserve Volume (ERV) [8,9]. Reduced lung volumes in obesity may result in reduced peripheral airway diameter, which subsequently may disturb smooth muscle function and potentially increase airway obstruction and Bronchial Hyper-Responsiveness (BHR) [8]. A second theory that has received growing attention is the effect of obesity on asthma via inflammatory pathways [7,10]. The chronic inflammatory process created by excess adiposity has been implicated as being an underlying factor in asthma pathogenesis. An increase in fat mass is associated with an increase in systemic inflammatory mediators which can exacerbate airway inflammation via inflammatory mediators such as leptin, adiponectin, Interleukin-6 (IL-6) and Tumour Necrosis Factor-alpha (TNF-α) [7,10]. Several studies noted that the pro-inflammatory effects of serum leptin can modulate airway inflammation [7,11,12].

In addition to those theories, multiple factors are studied which possibly play a role in the asthma-obesity relationship such as dietary factors, a sedentary lifestyle, genetic predisposition, metabolic abnormalities and associated comorbidities such as gastro-oesophageal reflux disease and sleep apnoea [4]. It is most likely that these influential factors and theories are not mutually exclusive, but altogether explain the relationship between asthma and obesity [12].

As obesity has a major impact on several asthma parameters, the effect of weight reduction in obese asthmatic children could be of great value for current treatment guidelines. Studies in adults concerning weight loss and its effect on asthma are promising [13-15]. Significant improvements have been found on asthma control, lung function, exacerbations and use of asthma medication after weight loss [14]. In children, the effects of weight loss have been hardly studied. As the obese asthmatic child is becoming more common in the clinical setting, there is need for a well-designed randomised controlled trial (RCT) in which the effects of weight reduction on asthma in children are studied.

### Objective and hypothesis

The Mikado study is an RCT in which the effects of an 18-month multifactorial intervention, on several asthma parameters and anthropometric outcomes in children with asthma and overweight are studied. We hypothesise that a multifactorial intervention will decrease the Body Mass Index –Standard Deviation Score (BMI-SDS) of children with asthma and overweight and will improve asthma related parameters including lung function, airway inflammation, asthma control and the use of asthma medication.

### The primary research question is

What are the effects of an 18-month multifactorial intervention on FEV_1_%predicted and BMI-SDS?

### The secondary research questions are

– What is the effect of a multifactorial intervention on the severity and control of asthma as indicated by lung function (FEV_1_/FVC, ERV), asthma symptoms, asthma control, asthma-related quality of life, Exercise Induced Bronchoconstriction (EIB), use of asthma medication and exacerbations?

– What are the underlying mechanisms? Is the intervention accompanied by decreased levels of adipokines and diminished airway inflammation? Can we detect a beneficial effect on airway mechanics/lung function?

– What are the potential moderators and mediators of the intervention effects (e.g. anthropometric changes, changes in physical activity and dietary behaviour, socio economic status, comorbidities and smoking exposure)?

## Methods/design

### Study design

The study design is an RCT for children with overweight and asthma (Figure 1). Children aged 6–16 years living in Southern Limburg, the Netherlands will be recruited. After a screening visit, participants will be randomised into an intervention group or a control group (Figure 1). The intervention group will receive an intervention lasting for 18 months (see details below), while the control group will receive standard usual care according to the standards of the Dutch Society of General Practitioners and the Paediatric Pulmonology section of the Dutch Society of Paediatrics [16,17].

**Figure 1 F1:**
[figure not shown]
**Flow diagram study design.** Abbreviations: BHR = Bronchial Hyper-Responsiveness, BMI = Body Mass index, EBC = Exhaled Breath Condensate, FeNO = Fractional exhaled Nitric Oxide, VO_2max_ = Maximal Oxygen Uptake.

Regular measurements including lung function outcomes, anthropometric outcomes, inflammatory outcomes and intervention mediators and moderators will be performed at baseline (T=0), after 6 months (T=6), 12 months (T=12) and at the end of the intervention (T=18). Every 3 months, participants will receive various questionnaires (Table 1). All procedures and materials are approved by the Medical Ethic Committee of Maastricht (MEC 09-2-088).

**Table 1 T1:** Overview of measurements per visit

	**Baseline**	**T3**	**T6**	**T9**	**T12**	**T15**	**T18**
**Lung function parameters**							
MEFV curves: FEV_1_, FVC, FEV_1_/FVC, PEF, MEF_50_ (absolute and %predicted values)^*^	X		X		X		X
Static lung function test: TLC, RV, FRC, ERV	X						X
BHR	X						
Maximum Ergometry test: VO_2max,_ HR_max_, %fall in FEV_1_	X						X
**Inflammatory parameters**							
FeNO	X						X
EBC: pH, IL-1α, 2, -4, -5, -10, -13, TNF-α, sICAM-1	X						X
Serum: leptin	X						X
**Questionnaires**							
PAQLQ verbal questionnaire for 6–11 year, written questionnaire for 12–16 year	X		X		X		X
EQ-5D-Youth questionnaire	X	X	X	X	X	X	X
c-ACT questionnaire for 6–11 year, ACT questionnaire for 12–16 year	X		X		X		X
ISAAC questionnaire + additional questions about symptoms and exacerbations. Parental version for 6–11 year, self-administered version for 12–16 year	X		X		X		X
GERD questionnaire. Parental version for 6–11 year, self-administered version for 12–16 year	X	X	X	X	X	X	X
PSQ questionnaire. Parental version for 6–11 year, self-administered version for 12–16 year	X		X		X		X
c-DEBQ questionnaire version for 6–11 year, DEBQ for 12–16 year	X						X
SDQ questionnaire. Parental version for 6–11 year, parental and self-administered version for 12–16 year					X		
Demographic factors: e.g. smoking, pets, parental educational level and BMI	X						X
Medication use	X	X	X	X	X	X	X
Health care utilization	X	X	X	X	X	X	X

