### Randomisation

All children who meet the inclusion criteria after the screening visit will be randomised to either the control or intervention group. Generalised block randomisation including 10 participants per block will be performed by a computer program, with an allocation ratio of 1:1 [23]. Because this is a lifestyle study, blinding is not possible.

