#### Questionnaires

Information on socio-demographic characteristics such as age, sex, ethnicity, parental BMI, social economic status and smoking exposure will be collected. Asthma control will be measured by the Asthma Control Test (ACT) in children >11 years [32]. The childhood ACT (C-ACT) will be used in children ≤11 years [32,33]. A score of ≤19 will be defined as uncontrolled asthma [34]. Medication use will be evaluated over the 2 months period prior to the clinic visit and dose equivalents will be calculated according to standard dosage of SABA, LABA and ICS [16,17,35,36]. The GINA guidelines will be used to determine asthma severity (intermittent, mild, moderate and severe) based on the intensity of treatment [37]. A Dutch questionnaire and the ISAAC questionnaire will be used to measure asthma symptoms [38]. Asthma-related quality of life will be measured by the Paediatric Asthma Quality of Life Questionnaire (PAQLQ) [39]. According to the PAQLQ guidelines, the minimal important difference will be defined as a difference of 0.42 points [40]. The Euroqol 5D Youth version will be used as a measurement tool for general health related quality of life [41].

To investigate commonly associated morbidity in children with asthma, sleep related breathing disorders will be assessed by means of the Paediatric Sleep Questionnaire (PSQ) [42]. A score of >0.33 will be defined as having a high risk for developing a sleep-related breathing disorder [42]. The existence of Gastro-Oesophageal Reflux Disease (GERD) symptoms will be assessed by the GERD questionnaire [43]. A suspicion of GERD is present when the score is ≥ 3 points [43]. Psychosocial problems will be determined by an abnormal score on the Dutch version of the Strength and Difficulties Questionnaire (SDQ) according to the SDQ scoring guidelines [44]. In addition, the Dutch Eating Behaviour Questionnaire (DEBQ) will be used to determine whether children have high scores on the subscales: Emotional Eating (13 items), External Eating (10 items) or Restrained Eating (10 items) [45].

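### The SDQ is scheduled at T12 only, so psychosocial problems have no pre-randomisation value and cannot serve as a baseline moderator or yield change from baseline

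*Protocol article*

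**What the plan says.** In Table 1, under Questionnaires, the row "SDQ questionnaire. Parental version for 6–11 year, parental and self-administered version for 12–16 year" is marked at T12 and nowhere else. The Questionnaires section of the text states: "Psychosocial problems will be determined by an abnormal score on the Dutch version of the Strength and Difficulties Questionnaire (SDQ"). That sentence belongs to a paragraph that opens "To investigate commonly associated morbidity in children with asthma" and also introduces the sleep questionnaire (PSQ) and the reflux questionnaire (GERD).

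The third secondary research question asks "What are the potential moderators and mediators of the intervention effects", and its list of examples includes "socio economic status, comorbidities and smoking exposure". Below Figure 1, the Study design section says that measurements including "intervention mediators and moderators will be performed at baseline (T=0), after 6 months (T=6), 12 months (T=12") and at the end of the intervention.

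**The concern.** A moderator is a characteristic that children bring to the trial, and it must be fixed before treatment can act on it. The intervention runs for 18 months, so T12 falls two thirds of the way through. By then the intervention arm has had cognitive behavioural sessions that cover bullying, self-esteem, emotions and social skills (Lifestyle sessions section). An SDQ score at T12 may therefore be partly a result of treatment. Grouping children by it would compare intervention and control children who were not alike at randomisation.

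The question at stake is whether children with psychosocial problems respond differently to the programme. Without a baseline score it cannot be answered, and no later analysis plan can recover a value that was never collected.

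**Working it through.** **1. The schedule.** The SDQ row has eight cells, matching the header (label, Baseline, T3, T6, T9, T12, T15, T18). The only X is under T12, so the row is not a broken table. Every other questionnaire row has at least Baseline and T18. Across all visit-scheduled rows of Table 1, the SDQ is the only one without a baseline mark. PSQ and GERD, its companions in the morbidity paragraph, both have one.

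**2. T12 score as moderator.** The documents give no figures for this, so all inputs here are assumptions. Let b be the baseline SDQ and u an independent later influence, both standard normal. Let t be the arm (0 or 1).
- T12 score: S = 0.7b + √0.51·u + shift·t. A child is abnormal if the score exceeds 1.
- Outcome: Y = 5t − 3u − b + noise. The true effect is 5.0 in every child, with no moderation.

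Results from 2,000,000 simulated children:

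| Treatment shift in T12 SDQ | Subgroups by | Effect, not abnormal | Effect, abnormal | Interaction |
|---|---|---|---|---|
| 0 | Baseline | 5.01 | 5.00 | −0.01 |
| 0 | T12 | 5.01 | 4.97 | −0.05 |
| −0.5 SD | Baseline | 5.02 | 4.98 | −0.04 |
| −0.5 SD | T12 | 4.58 | 3.85 | −0.73 |

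T12 subgroups produce a false interaction when treatment shifts the SDQ and the SDQ shares causes with the outcome. They do not when treatment leaves the SDQ alone. Baseline subgroups are sound in both cases.

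**3. Between-arm comparison at T12.** The documents state no power for the SDQ, so there is no figure to reproduce. The inputs are borrowed from the FEV1 calculation in the Sample size calculation section: 104 children, 1:1, 5% drop-out, two-sided 5%, 80% power, correlation 0.7. Applying 0.7 to the SDQ is an assumption.
- Per arm: 104 × 0.95 / 2 = 49.4, taken as 49.
- Detectable difference without baseline: (1.960 + 0.842) × √(2/49) = 2.802 × 0.202 = 0.57 SD.
- With baseline adjustment, multiply by √(1 − r²). For r = 0.7: 0.566 × 0.714 = 0.40 SD. For r = 0.5: 0.49 SD. For r = 0.8: 0.34 SD.
- With 20% drop-out (104 × 0.80 / 2 = 41.6, taken as 42): 0.61 SD without, 0.44 SD with adjustment at r = 0.7.
- Power for a 0.5 SD difference, 49 per arm: about 70% without, 93% with adjustment at r = 0.7.

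In 20,000 simulated trials of 49 per arm analysed at T12 without any baseline, the type I error was 5.2% (nominal 5%). A true difference of −0.50 SD was estimated at −0.50 on average.

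**The case against.** A reader might infer that, with no baseline, the SDQ cannot show an intervention effect because a T12 difference could be a chance imbalance present from the start. The documents do not support that. Children are randomised "with an allocation ratio of 1:1", and the significance level of a randomised comparison already allows for chance imbalance. The loss is in precision, not validity. Psychosocial problems are also not named as an outcome of the intervention.

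Other points on the plan's side:
- **The moderator role is inferred.** Neither the SDQ nor psychosocial problems is named as a moderator. The reading joins the general word comorbidities in the research question to the morbidity paragraph. This stands as a qualification, although it is the natural reading. PSQ and GERD can still serve as comorbidity moderators.
- **A mediator should be measured after randomisation.** T12 precedes the T18 endpoint, so mediator use is possible and a missing T18 score is no defect on that reading. A single administration can also describe how common abnormal scores are. Both stand; mediation is weaker without a baseline.
- **The Study design sentence is a general summary.** FeNO, breath condensate, leptin, static lung function and ergometry also skip the middle visits, and hyper-responsiveness is measured at baseline only. This is fair, but each of those rows keeps its baseline value. Only the SDQ row lacks it.
- **The bias is conditional.** It vanishes if treatment does not move the SDQ. That is correct, but the programme works on related problems, and without a baseline score the condition cannot be relied on.

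**Conclusion.** The point holds in limited form. Psychosocial problems have no pre-randomisation value, so they cannot be used as a baseline moderator and change from baseline cannot be estimated. The single T12 mark also sits badly with the protocol's own statement that moderators and mediators are measured from baseline.

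Under the assumed 0.5 SD treatment shift, T12 subgroups would show a false interaction of about −0.7 against a true uniform effect of 5.0. Its size depends wholly on the assumed shift and shared causes. For the T12 comparison of arms, the price is a detectable difference of about 0.57 SD instead of 0.40 SD, assuming 49 per arm and a correlation of 0.7.

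The matter concerns a secondary question and touches neither primary outcome.

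**What to change.** Add the SDQ to the baseline column of Table 1, or correct the table if the mark is simply misplaced. Use only the baseline score as a moderator, and adjust the T12 score for it in any comparison of arms. For children already enrolled without a baseline score, leave the SDQ out of the moderator analysis rather than substituting the T12 score. A T18 administration is optional.

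The cost is one short questionnaire at a visit that already takes place, with a small added burden on parents and children. Delay has its own cost, since each child enrolled before the change is lost to the SDQ moderator question.

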**Anthropometric values**							
Weight	X	X^i^	X	X^i^	X	X^i^	X
Length	X	X^i^	X	X^i^	X	X^i^	X
Waist and hip circumference	X		X		X		X
4-fold Skinfold measurement	X		X		X		X
**Intervention outcome measures**							
3 × 24 hour food record	X	X^i^	X		X		X
7 days accelerometer output	X	X^i^	X		X		X
**Continuously measured parameters**							
Percentage presence during the sport sessions, lifestyle sessions, parental sessions and individual counselling sessions. Average heart beat during the sport sessions, BORG score of fatigue [59] after the sport sessions, motivation of the participants (1–10) rated by the sport instructor after the sport sessions, amount of asthma attacks during sporting and safety of the participants.							

Legend: * Pre- and post-bronchodilator spirometry will be obtained during every visit to determine reversibility. At baseline, reversibility will be determined after the BHR test. X^i^ = Data only obtained in the intervention group.

Abbreviations: *ACT*, Asthma control test; *BHR*, Bronchial hyper-responsiveness; *BMI*, Body mass index; *BORG*, Perceived exertion and pain scale; *c-ACT*, Childhood asthma control test; *c-DEBQ*, Childhood dutch eating behavioural questionnaire; *DEBQ*, Dutch eating behavioural questionnaire; *ERV*, Expiratory reserve volume; *EQ-5D-Youth*, Youth version of Euroqol 5D quality of life questionnaire; *FEV*_*1*_, Forced expiratory volume in 1 second; *FRC*, Functional residual capacity; *FVC*, Forced vital capacity; *GERD*, Gastro oesophageal reflux disease; *HRmax*, Maximum heart rate; *IL*, Interleukin; *ISAAC*, International study of asthma and allergy in childhood; *MEF*_*50*_, Maximum expiratory flow rate at 50% of vital capacity; *PAQLQ*, Paediatric asthma quality of life questionnaire; *PEF*, Peak expiratory flow, *pH*, Acidity; *PSQ*, Paediatric sleep questionnaire; *RV*, Residual volume; *SDQ*, Strengths and difficulties questionnaire; *sICAM-1*, Soluble intercellular adhesion molecule-1; *TLC*, Total lung capacity; *TNF-α*, Tumour necrosis factor-alpha; *VO*_*2max*_, Maximal oxygen uptake.

### Recruitment

Children will be recruited from 4 sources. The first source is a community-based random online questionnaire to parents of 40,000 children in Southern Limburg. The second source includes pulmonary paediatricians of 3 local hospitals. Thirdly, children are recruited via the youth section of the Municipal Health Services in Southern Limburg. Additionally, children are recruited via cohorts of several other studies [18,19].

All parents will be asked to fulfil an online questionnaire about anthropometric values and asthma symptoms. Children who are overweight according to the parental reported BMI and who reported current asthmatic symptoms and/or use of asthma medication will be invited for a screening visit. Written informed consent will be obtained from all parents and from children aged 12 years or older.

### Eligibility criteria

All children with asthma and overweight, aged 6–16 year, living in Southern Limburg will be invited to participate. Overweight will be defined as a BMI-SDS >1 according to the Lambda Mu and Sigma (LMS) method of Cole et al. [20] based on the reference charts of the Dutch fourth Nationwide Growth Study [21]. During the screening visit, participants will undergo lung function measurements to verify the diagnosis of asthma. A child will be considered asthmatic if at least 2 of the 3 following criteria are fulfilled: 1. asthmatic symptoms in the previous 12 months based on the International Study of Asthma and Allergy in childhood (ISAAC) questionnaire [22]; 2. use of Short Acting Beta2agonists (SABA), Long Acting Beta2agonists (LABA) or Inhaled Corticosteroids (ICS) in the previous 6 months; 3. reversibility; defined as an increase of ≥9% of the predictive value of the FEV_1_ after inhalation of 400 μg Airomir (Teva Pharma, Leiden, the Netherlands) or a positive BHR test; defined as a histamine concentration of ≤8 mg/ml necessary to provoke a drop of 20% in FEV_1_.

Children will be excluded in the case of a congenital malformation of the airways or other chronic lung diseases, syndromes accompanied by mental retardation or metabolic diseases, physical limitations to exercise, and/or a heart disease.

